#### Qualitative methods

Interviews with children and parents will be analyzed using inductive qualitative content analysis. Interviews will be audio-recorded and transcribed verbatim. Meaning units adhering to the aim will be extracted, condensed, and coded. The codes will be categorized according to similarities and differences and will be further grouped into subcategories and categories. Both manifest and latent content may be analyzed [78, 79].

#### Mixed methods

The implementation process will be analyzed with a convergent parallel mixed method [80] that includes both descriptive statistics and qualitative content analysis of implementation outcomes, barriers, and facilitators in routine clinical practice, and treatment adherence, patterns of treatment use, and treatment changes over time. This includes continued use, discontinuation, switching between treatments, and combined use of a weighted blanket and melatonin from the perspectives of clinical staff, children and parents. Changes in clinical routines, staffing, and implementation procedures over time will be documented and considered as contextual factors in the process evaluation and interpretation of the long-term findings.

The implementation evaluation will combine an implementation outcomes framework, a process evaluation framework, and a determinants framework. Proctor’s Implementation Outcomes Framework [81] will be used to conceptualize relevant implementation outcomes, including acceptability, feasibility, fidelity, reach, implementation cost, and sustainability, where applicable. Moore et al.’s process evaluation framework [82] will be used to structure process-related components of the evaluation, including fidelity, dose, reach, recruitment, exposure, adherence, and satisfaction. Contextual determinants, including barriers and facilitators, will be analyzed using the Consolidated Framework for Implementation Research (CFIR) as a determinants framework [83] (Table 2).

Intervention: Characteristics of the intervention, e.g., perceived adaptability and complexity for use in routine practice.External environment: Characteristics of the external environment, e.g., patient needs, resources, external policies and incentives.Internal environment: Characteristics of the environment in which the intervention is implemented, e.g., structural characteristics and culture.Individual domain: Characteristics of the clinical staff members delivering the intervention, e.g., knowledge, attitudes and confidence regarding the intervention being implemented.Implementation process: The activities and strategies used to support the implementation of the intervention, e.g., planning and execution.

**Table 2 Tab2:** Evaluation of implementation outcomes, process components, and contextual determinants

	Questions about the evaluation of the intervention	Data collection	Data analysis
1. Fidelity	To what extent was the intervention implemented as planned?	Interviews with clinical staff.	Descriptive analysis.
2. Dose	To what extent was the weighted blanket intervention delivered in routine clinical practice?	Clinical staff and researcher checklist (documentation of sleep problems in children and the number of those who were offered and agreed to participate in the research project).	Descriptive analysis.
3. Reach	To what extent were eligible children and families reached and included in the research project?	Clinical staff and researcher checklist and follow-up every 3 months. Individual interviews and/or focus groups with clinical staff.	Descriptive analysis.
4. Recruitment	How were children and families recruited to the sleep intervention?	Clinical staff and researcher checklist and follow-up every 3 months. Individual interviews and/or focus groups with clinical staff.	Descriptive analysis.
5. Exposure, adherence, and satisfaction	To what extent did children continue, discontinue, switch, or combine treatments during follow-up? Did children, parents, and clinical staff find the sleep intervention acceptable and satisfactory?	Clinical staff and researcher checklist. Parent-reported use of weighted blanket and/or melatonin. Individual interviews and/or focus groups with clinical staff, parents and children.	Descriptive analysis. Categories identified through content analysis.
6. Implementation cost	What costs and resources were associated with implementing the weighted blanket intervention and standard melatonin treatment?	Data on costs of prescription of weighted blankets or melatonin, purchase prices, administrative costs, and clinical staff time	Descriptive analysis.
7. Context	What barriers and facilitators influenced implementation of the sleep intervention? The five CFIR domains concern characteristics of: 1. Intervention 2. External environment 3. Internal environment 4. Individuals 5. Implementation process	Individual interviews and/or focus groups with clinical staff, parents and children at 6 and 12 months.	Categories identified through content analysis.

Implementation outcomes are informed by Proctor’s Implementation Outcomes Framework [81]; process-related components are structured according to Moore et al.’s process evaluation framework [82]; and contextual determinants, including barriers and facilitators, are based on the Consolidated Framework for Implementation Research (CFIR) [83]

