## Methods

### Study design

The research project uses a pragmatic prospective longitudinal cohort design with two initial treatment arms: a weighted blanket intervention and standard melatonin treatment. Treatment selection will be based on family preference and clinical decision-making in routine clinical practice rather than randomization. Child-parent dyads will be followed from baseline to 12 months, with annual long-term follow-ups for an additional nine years. The rationale for the long-term follow-up is to capture children’s development from childhood through adolescence and into young adulthood. The main evaluation of real-world changes in sleep, treatment adherence, health-related outcomes and resource utilization will focus on the first 12 months after inclusion, whereas the annual long-term follow-ups will be exploratory and used to describe longer-term patterns of treatment use, adherence, treatment changes, sleep, health-related outcomes, and resource utilization. Treatment changes may include continued use, discontinuation, switching between treatments, and combined use of weighted blankets and melatonin. The cohort study is combined with a process evaluation and uses a hybrid type 1 effectiveness–implementation approach [32, 33], in which clinical outcomes are the primary focus and implementation outcomes and contextual determinants are explored in parallel. Quantitative, qualitative, and mixed methods will be used.

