The sleep problems screening form is completed by parents and consists of three items from the Swedish version of the Children’s Sleep Habits Questionnaire (CSHQ-SWE) [36, 37]. Each item is scored in terms of 0–1, 2–4, or 5–7 days per week. The items are: “Child falls asleep within 20 minutes after going to bed” (scoring criteria 0–1 or 2–4 days per week), “Child sleeps too little” (scoring criteria 2–4 or 5–7 days per week), and “Child awakes more than once during the night” (scoring criteria 2–4 or 5–7 days per week). Each item contains the follow-up question: “Is this a problem?” (yes / no). If at least one of the items fulfills the scoring criteria and is indicated to be a problem, the child is considered eligible for inclusion.

At the follow-up visit, the sleep problems screening form is assessed by a nurse. If the child fulfills the inclusion criteria of ADHD diagnosis, sleep problems, age 6–14 years, and is a patient at the ADHD unit, and if the child-parent dyad understands written and spoken Swedish, the child-parent dyad is invited to participate in the research project.

Recruitment to the research project will occur continuously and include both newly and previously diagnosed children at the unit, and those who use and do not use ADHD medication. Participants will enter one of two initial treatment arms: (1) weighted blanket or (2) standard treatment with melatonin. During follow-up, participants may continue their initial treatment, discontinue treatment, switch between weighted blanket and melatonin treatment, or use the two treatments in combination, based on family preference and clinical decision-making. Treatment use and treatment changes over time will be documented as part of the pragmatic evaluation.

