### Intervention

The weighted blankets are fibre blankets (Novista.se) which distribute the weight evenly across the body, in comparison with other weighted blankets, such as ball blankets [38] or chain blankets [39], where the pressure is concentrated on certain points on the body [38, 39]. Children included in the research project receive a weighted blanket (4 kg, 6 kg, 8 kg, or 10 kg) with weight based on age, body weight, and degree of sleep problems, according to a specifically designed manual that follows practice for prescribing blankets. Melatonin will start at 1 or 2 mg, with a dose range up to 6 mg.

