###### Checklist

A checklist will be maintained by clinical staff and researchers in the project to evaluate the extent of implementation, accessibility and recruitment of participants, and treatment use over time, including continued use, discontinuation, switching between treatments, combined use of weighted blankets and melatonin, and withdrawal from the study.

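### Table 2 defines the Dose of the weighted blanket by enrolment in the project, which covers both arms and so does not identify blanket delivery

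*Protocol article*

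**What the plan says.** Table 2 (Mixed methods) lists dose, reach and recruitment as separate components of the process evaluation.

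- **Row 2, Dose.** The question is "To what extent was the weighted blanket intervention delivered in routine clinical practice". The source is the checklist kept by clinical staff and researchers, and a bracket says what is taken from it: "documentation of sleep problems in children and the number of those who were offered and agreed to participate in the research project". The analysis is descriptive.
- **Row 3, Reach.** The question is "To what extent were eligible children and families reached and included in the research project". The source is the same checklist with three-monthly follow-up, plus staff interviews or focus groups.
- **What joining means.** Under Participants and recruitment, "Participants will enter one of two initial treatment arms: (1) weighted blanket or (2) standard treatment with melatonin". Under Study design, "Treatment selection will be based on family preference and clinical decision-making in routine clinical practice rather than randomization".
- **What else is recorded.** The Checklist section gives that tool a wider scope than the bracket in row 2: "extent of implementation, accessibility and recruitment of participants, and treatment use over time, including continued use, discontinuation, switching between treatments". Parents report how many nights a week the blanket or melatonin is used, and Table 2 places this in row 5. Prescribed drugs come from the health records (School absence and healthcare consumption).
- **The blanket itself.** Under Intervention, the weight is chosen "according to a specifically designed manual that follows practice for prescribing blankets".

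**The concern.** The question in row 2 and the data in row 2 concern different things. The question is about one product reaching children. The data count families who were invited to, and joined, a project with two treatments. A child who joins and starts melatonin adds one to the Dose count without having received a blanket.

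Because the arm is not randomized, the blanket share among joiners is an outcome of the study. It is not a known constant by which the enrolment count could be rescaled. That share is part of what an implementation study of the blanket should report, and the row 2 indicator cannot show it.

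Implementation of the blanket in routine practice is a stated aim, and the Discussion says the authors know of no earlier study of that process. If the row is followed as written, the figure reported as Dose will describe recruitment, and a reader could take good recruitment for good blanket delivery.

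**Working it through.** **The plan's own figure.** Row 2 states no number, so there is none to reproduce. The article's sample size of 64 per group does reproduce (a two-sided t test with d = 0.50 and alpha 0.05 has power 0.801 at 64), but it has no bearing on this point.

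**Inputs from the article.** Planned enrolment is 150 per initial arm, 300 in total (Statistical power). About 175 children a year are expected to screen positive (Participants and recruitment).

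**Inputs assumed, because the article gives neither.** The number agreeing per year, A, is taken as 100 or 150. The share of joiners who start with a blanket, p, is taken as 10%, 50% or 90%.

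**Formulas**, per screen-positive child:

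- Row 2 indicator = A / 175
- Blanket started = A × p / 175

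| A (assumed) | Row 2 indicator | Blanket, p = 10% | Blanket, p = 50% | Blanket, p = 90% |
|---|---|---|---|---|
| 100 | 100/175 = 57.1% | 10/175 = 5.7% | 50/175 = 28.6% | 90/175 = 51.4% |
| 150 | 150/175 = 85.7% | 15/175 = 8.6% | 75/175 = 42.9% | 135/175 = 77.1% |

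Across each line the indicator does not move, while the share starting with a blanket changes nine-fold (90%/10%). The indicator carries no information on p.

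**At the planned totals.** The count agreeing is 300 and the count starting with a blanket is 150, so the ratio is 300/150 = 2.0. It needs no assumption about how many families are offered the project. It refers to the initial treatment only. The design allows switching and combined use, so some melatonin starters may receive a blanket later, and the ratio to children who ever received one would then be lower. At the extreme where all 150 did so, it would be 300/300 = 1.

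**Overlap with Reach.** Row 2 counts offers and agreements among children with documented sleep problems. Row 3 asks about reach and inclusion among eligible families. A documented sleep problem is one of the eligibility conditions, and agreeing to take part is inclusion. The numerators describe the same event, while the denominators may differ through the remaining eligibility criteria.

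**The case against.** The best case for the plan has several parts.

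- **The checklist is broader than the bracket.** It also covers the extent of implementation and treatment use over time, so the team could derive blanket delivery from it. This stands, and it limits the fault to how the indicator is defined. It does not remove the fault, because row 2 itself says which items it will use.
- **Joining is the expected route to a blanket.** The Background reports a Swedish recommendation that blankets for sleep problems be prescribed only within research. Offers and agreements are therefore a relevant upstream step. That stands too, but without a split by arm they stop short of delivery.
- **The two-fold ratio arises only if nobody splits by arm.** This is correct. Initial arm is known for every child, and the ratio describes row 2 as written, not an unavoidable result.
- **Article format.** A condensed article may leave checklist fields to a fuller document, so the absence of fields such as delivery date is not held against it. The point here is different: the article does name an indicator, and that indicator does not answer the row's question.

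Three stronger readings are tempting, and the documents do not support them.

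1. A reader might infer that a null CSHQ result could not be traced to under-delivery. Adherence and treatment changes are a primary outcome area, parents report nights of use, the checklist follows use and switching, and prescriptions are drawn from records. Low exposure can be examined without row 2.
2. A reader might infer that Dose and Reach will be numerically identical. Row 3 fixes no number and adds interviews, so only substantial overlap can be claimed.
3. A reader might infer that Fidelity is also deficient because it rests on staff interviews. That is a stated choice within a mixed-methods evaluation.

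**Conclusion.** The point holds in a limited form. The Dose indicator in Table 2 measures project enrolment across both arms. It does not measure delivery of the weighted blanket, and it largely repeats Reach.

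At the planned totals, unsplit enrolment is twice the number starting with a blanket. That factor rests on the equal arm targets being met and on counting initial treatment only. The percentages in the table above are illustrations that depend on assumed uptake and blanket share.

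The consequence is confined to one descriptive process measure in a design where clinical outcomes come first. The CSHQ analysis and the sample size are not affected, and most of the data needed for a correct indicator are already planned. It is worth correcting because the change is cheap and alters the figure that would be reported as Dose.

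**What to change.** In Table 2, row 2, replace the bracketed indicator with the number and share of children with documented sleep problems who (a) were offered a weighted blanket, (b) accepted it and (c) actually received it. Take these from the existing checklist and report them by initial arm, so that blankets received later by children who started on melatonin are visible. Preferably record the blanket weight supplied as well.

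Leave the counts of families offered and agreeing to the project in rows 3 and 4, and leave nights of use in row 5, so that each row measures one thing. Fidelity in row 1 needs no change on this account.

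The cost is an edit to one table row and one or two fields on a checklist that is already kept. The fields should be added early, since a handover that was not recorded at the time is harder to reconstruct later. Nothing changes in treatment, recruitment, questionnaires or the main analysis.

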## Discussion

Weighted blankets have demonstrated potential to reduce perceived sleep problems [27, 29, 30]; however, to the best of our knowledge, no study has previously explored the process of implementing a weighted blanket intervention in clinical practice for children with ADHD and sleep problems. There is also a knowledge gap concerning real-world effectiveness, longer-term patterns of treatment use, adherence, and treatment changes, and implementation of a weighted blanket intervention and standard melatonin treatment in routine clinical practice. This research project will address these gaps by following sleep-related outcomes, treatment adherence, health-related outcomes, resource utilization, and treatment changes, including continued use, discontinuation, switching between treatments, and combined use of weighted blankets and melatonin, within and across the initial treatment arms over time. The results will inform future evaluation of treatment options for children with ADHD and sleep problems and support the implementation of weighted blanket interventions in clinical practice. Moreover, the assessment of various aspects of the health of children and their parents will add to knowledge on how the child’s ADHD diagnosis combined with sleep problems affects the family in their everyday lives.

Methodological considerations need to be discussed. A strength of the research project is that it includes both questionnaires and interviews. The questionnaires capture diverse and broad outcomes and will be answered by both children and parents. Moreover, the multi-informant design of interviews ensures that children’s, parents’ and clinicians’ perspectives are taken into consideration, strengthening the generalizability and applicability in clinical settings and everyday life. The use of quantitative, qualitative, and mixed methods ensures rich data, which could support validity of results.

A methodological challenge is to ensure participation in the longitudinal follow-ups. The battery of questionnaires is extensive, and follow-ups are frequent during the first year, which may reduce participants’ willingness to continue participating. To address this, each parent will be contacted by the research team at recruitment by phone so questions can be answered, aims revisited, and the importance of adherence can be emphasized.

A limitation of this research project is that some outcome measures will be administered outside their validated age ranges. This pragmatic approach reflects the broad age range of eligible participants, the continuous recruitment, and the relatively long follow-up period of the study cohort, allowing the use of a consistent assessment battery throughout the study. The selected instruments assess constructs that are considered theoretically relevant across the included age span. However, as their psychometric properties have not been established for all ages included, findings from participants outside the validated age ranges should be interpreted with caution and considered exploratory. Although the CSHQ total score has been specified as the primary sleep outcome for the main effectiveness evaluation, additional sleep-related measures are included to capture different aspects of sleep across the broad age range and follow-up period. As children grow older, more emphasis will be placed on self-reported instruments rather than proxy-reported instruments. However, the use of both proxy-reported and self-reported sleep measures throughout the study period allows overlap between perspectives and may strengthen comparisons over time. Another possible limitation is that sensory profiles will not be assessed by a specific measure. As the study incorporates multiple questionnaires, compromises are necessary to balance data collection needs with participant welfare. In consideration of the sensitive nature of the study population, the aim is to minimize respondent burden and avoid imposing excessively lengthy assessment protocols. Participants will be asked about their sensory impressions in interviews, which will enable in-depth information that may increase understanding of the sensory aspects of weighted blanket use for children with ADHD.

The research project, rooted in clinical practice, aims to inform clinical guidelines and decision-making frameworks for personalized ADHD care. Grounded in the real-world clinical setting, it is highly relevant to healthcare systems. By exploring the implementation of weighted blankets as a non-pharmacological treatment, the project may promote a multimodal approach to management of sleep problems in children with ADHD. This approach may provide families and healthcare professionals with a non-pharmacological treatment option alongside standard melatonin treatment.

## Data Availability

No datasets were generated or analysed during the current study.

## Abbreviations

ADHD: Attention-deficit/hyperactivity disorder
ANCOVA: Analysis of Covariance
BCFPI: Brief Child and Family Phone Interview
CAMHS: Child and Adolescent Mental Health Service
CFIR: Consolidated Framework for Implementation Research
CORS: Child Outcome Rating Scale
CSHQ: Children’s Sleep Habits Questionnaire
CSHQ-SWE: Children’s Sleep Habits Questionnaire – Swedish version
DSM: Diagnostic and Statistical Manual of Mental Disorders
HBSC: Health Behaviour in School-aged Children
ISI: Insomnia Severity Index
ORS: Outcome Rating Scale
ODD: Oppositional Defiant Disorder
PISI: Pediatric Insomnia Severity Index
R-ANCOVA: Repeated Measures Analysis of Covariance
R-ANOVA: Repeated Measures Analysis of Variance
SNAP-IV: Swanson, Nolan, and Pelham Scale IV
SSR: Sleep Self-Report
STAI: State-Trait Anxiety Inventory Scale
TIC-P: Treatment Inventory Cost in Psychiatric Patients
VAS: Visual analogue scale
WSAS-P: Work and Social Adjustment Scale, Parent version
WSAS-Y: Work and Social Adjustment Scale, Youth version
